## Abstract

**Background:**

Dysbiosis of gut microbiota plays a key role in type 1 diabetes mellitus (T1DM). Fecal microbiota transplantation represents a novel therapeutic avenue. We hypothesize that youth-derived fecal microbiota transplantation (yFMT) can remodel the gut microecosystem and improve clinical outcomes. This pilot trial aims to assess the feasibility, safety, and preliminary efficacy of yFMT in adults with T1DM.

**Methods and analysis:**

This single-center, randomized, double-blind, placebo-controlled pilot study will enroll adults with T1DM who have suboptimal glycemic outcomes (glycated hemoglobin [HbA1c] of 7.0–14.0% or time in range [TIR] <70%). Following a 17-day run-in period for insulin optimization, continuous glucose monitoring (CGM) wearing, baseline assessments and bowel preparation, participants will be randomly allocated (1:1) to take yFMT or placebo capsules for 6 consecutive days, alongside their standard insulin therapy, and then complete a 12-week follow-up. The primary efficacy endpoint is the change from baseline in the rate of achieving the composite target of TIR > 70% and time below range <4% at 12 weeks post-randomization. Secondary efficacy endpoints include: (1) the change from baseline in the same composite achievement rate at 4 weeks post-intervention; (2) changes from baseline at Weeks 4 and 12 in other glycemic metrics (including HbA1c, fasting plasma glucose, 2-hour postprandial glucose, and additional CGM metrics), C-peptide, immune responses, infection markers, and gut microbiota composition; and (3) changes from baseline at Week 12 in serum metabolomic profiles (bile acids, short-chain fatty acids, and other related metabolites). Feasibility will be assessed through recruitment rate, retention rate, intervention adherence, and acceptability. Safety endpoints include the incidence of adverse events and serious adverse events.

**Discussion:**

Our findings will offer new insight into the feasibility and effects of oral yFMT capsules in adults with T1DM and provide the necessary evidence to power a subsequent multicenter large-scale study. Exploratory biomarker analyses conducted within this study may further pave the way for future individualized microbiome‑based therapeutics.

**Trial registration:**

Chinese Clinical Trial Registry identifier: ChiCTR2500111955 (November 7, 2025).

## 1. Introduction

Type 1 diabetes mellitus (T1DM) is a chronic autoimmune disease characterized by the destruction of pancreatic β cells and lifelong insulin dependence [1]. Although advances in insulin analogs, delivery modalities, and continuous glucose monitoring (CGM) systems have improved diabetes management, people with T1DM still face challenges such as suboptimal glycemic outcomes, frequent episodes of hypoglycemia, and a high burden of self-management [2–7].

The core pathological mechanism of T1DM involves autoimmune-mediated destruction of pancreatic β cells. Conventional insulin therapy fails to halt the autoimmune process or restore β-cell function. In recent years, the gut microbiota, termed the “second genome,” has been recognized as an important contributor to T1DM pathogenesis [8]. Numerous studies have characterized gut microbiota alterations in individuals with T1DM, marked by a reduction in butyrate-producing bacteria and secondary bile acids, along with an increase in pathobionts [9–11]. Impaired intestinal barrier function represents another hallmark of this dysbiotic state, and together these features contribute to disruption of the “gut microbiota-intestinal-islet axis” [11].

Fecal microbiota transplantation (FMT) is a promising technique that transfers healthy donor microbiota to a recipient, aiming to restore microbial homeostasis. Evidence from animal studies has demonstrated that modulation of the gut microbiota can improve glycemic control through multiple mechanisms, including enhancement of intestinal barrier integrity, increased production of short-chain fatty acids, regulation of immune responses, and preservation of residual β-cell function [12,13].

Clinical evidence supports the potential of FMT in enhancing glycemic control among patients with T1DM. In a randomized controlled trial (RCT), both autologous and allogeneic FMT groups exhibited a reduction in glycated hemoglobin (HbA1c) at 12 months, without significant changes in insulin dosages [14]. Additionally, clinical studies demonstrate that washed microbiota transplantation significantly increases the time in range (TIR) and reduces glycemic variability among adults with T1DM [15,16]. Together with two capsule-based RCTs [17,18], these studies showed that FMT was generally safe, with mild and transient gastrointestinal symptoms being the most frequent adverse events [14–18].

Despite preliminary evidence supporting the potential of FMT to treat T1DM, several challenges remain: (1) studies primarily target β-cell function with inconsistent results, and lack assessment of autoimmunity or insulin sensitivity; (2) reliance on HbA1c or isolated CGM values, while composite target of TIR (3.9–10.0 mmol/L) >70% and time below range <3.9mmol/L (TBR3.9) <4% are seldom used; (3)donor screening lacks unified criteria, and techniques for preparation and delivery vary widely; and (4) the complex and poorly tolerated nasojejunal tube remains the primary administration method.

The youth-derived FMT capsules are prepared from rigorously screened healthy young donors (aged 4–17 years), selected for the relatively high temporal stability of the gut microbiota during this developmental window [19,20]. Our study pioneers the oral use of yFMT in a pilot RCT to evaluate the feasibility, safety, and preliminary efficacy of yFMT in adults with T1DM.

## 2. Methods

### 2.1. Study design

This pilot, randomized, double-blind, placebo-controlled trial conducted at Zhongnan Hospital of Wuhan University (China), is designed primarily to assess the efficacy, safety, and feasibility of yFMT in adults with T1DM. The schedule of activities to be performed and a study flowchart are provided in Figs 1
**and**
2. Participants will be randomized in a 1:1 ratio to receive either oral yFMT capsules or placebo capsules. The study will remain blinded until the database lock. Participants will provide written informed consent prior to enrollment.

**Fig 1 pone.0343078.g001:**
[figure not shown]
SPIRIT schedule of enrollment, intervention, and assessments. Note: Following informed consent on Day −17, candidates will undergo a 14-day CGM assessment and HbA1c testing (Day −3). Only those with HbA1c of 7.0–14.0% or CGM-derived TIR below 70% will be enrolled. Abbreviations: CGM, Continuous Glucose Monitoring; BP, Blood Pressure; P, Pulse; WC, Waist Circumference; BMI, Body Mass Index; WHR, Waist-to-Hip Ratio; TIR, Time in Range; TBR3.9, Time Below Range <3.9 mmol/L; Treg, Regulatory T cells; Th17, T helper 17 cells;.

**Fig 2 pone.0343078.g002:**
[figure not shown]
Flow chart of design. Abbreviations: CGM, Continuous Glucose Monitoring; yFMT, youth-derived fecal microbiota transplantation;.

### 2.2. Trial status

This study was approved by the Medical Ethics Committee, Zhongnan Hospital of Wuhan University (Ethics Approval No. 2025302) in October 2025. Recruitment started on November 20, 2025, and is ongoing, with completion expected by July 31, 2026. Data collection will conclude by November 30, 2026, with results expected by January 31, 2027.

### 2.3. Participants

Participant recruitment will be conducted from November 2025 to July 2026. Eligible participants aged 18–60 years must have a T1DM duration of more than one year and suboptimal glycemic outcomes, defined as HbA1c of 7.0–14.0% within the past three months or 14-day CGM-derived TIR < 70% within the past month. Participants will be excluded if they had recent episodes of diabetic ketoacidosis, concurrent severe gastrointestinal diseases, significant gastrointestinal surgery, pregnancy, or lactation. The diagnosis of T1DM adheres to the criteria established by the World Health Organization and the American Diabetes Association. Full criteria are listed in Table 1.

**Table 1 pone.0343078.t001:** Inclusion and exclusion criteria for enrollment.

Inclusion Criteria	
1	T1DM was diagnosed by an endocrinologist for at least 1 year
2	Aged 18–60 years (inclusive)
3	HbA1c between 7.0 to 14.0% (within past 3 months) or TIR < 70% (14-day CGM within the past month)
4	On MDI or insulin pump therapy for ≥3 months
5	TDD before admission ≥0.3 IU/kg/day, with a basal rate ≥0.05 IU/hour
6	Women of childbearing age are willing to use appropriate contraceptive measures
7	Signed informed consent form

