### 2.4. Procedures

#### 2.4.1. Screening (Day −17).

Screening (Day −17, Outpatient): Informed consent will be obtained, and eligibility will be assessed against all inclusion and exclusion criteria. Eligible participants will be provided with a CGM device.

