#### 2.4.2. Run-in Period and Baseline Assessments (Day −17 to Day 0).

This period standardizes participants’ status prior to intervention and consists of two phases:

*Outpatient Phase* (Day −17 to −3): Participants will wear CGM and undergo insulin dose optimization. During this period, participants are instructed to follow a standardized diet according to the Chinese Diabetes Dietary Guidelines (2017). Dietary adherence is monitored through food records and regular follow-up communications via WeChat or outpatient visits. CGM data from this phase serves as the baseline for glycemic metrics, including TIR, TBR3.9, glucose management indicator (GMI), coefficient of variation (CV), and other metrics.

*Inpatient Phase* (Day −3–0): Participants are hospitalized for baseline assessments and bowel preparation:

(1) Baseline Assessments (Completed by Day −3) include:a. Demographics and clinical parameters: age, sex, T1DM duration, anthropometrics (height, weight, waist-to-hip ratio [WHR]), vital signs (blood pressure, pulse), and comprehensive medical/medication history;b. Glycemic and lipid profiles: fasting plasma glucose, 2-hour postprandial glucose via Mixed-Meal Tolerance Test [MMT], HbA1c, total cholesterol (TC), triglycerides (TG), low-density lipoprotein cholesterol [LDL-c], and high-density lipoprotein cholesterol [HDL-c];c. β-cell function and insulin sensitivity (fasting/stimulated 2-hour C-peptide during Mixed-Meal Tolerance Test [MMT 2h CP], estimated glucose disposal rate [eGDR]);d. Diabetic autoantibodies: Glutamic Acid Decarboxylase Autoantibodies [GADA], Insulinoma-associated antigen-2 autoantibodies [IA‑2A], Islet cell autoantibodies [ICA];e. Inflammatory markers: white blood cell count [WBC], High-Sensitivity C-reactive protein [hs-CRP], erythrocyte sedimentation rate [ESR], procalcitonin [PCT], and cytokines [TNF-α, IL-1β, IL-8, IFN-γ];f. Intestinal Barrier-Related Antibodies: Anti-Lipopolysaccharide [Anti-LPS], Anti-Occludin;g. Immune marker: Treg/Th17 ratio;h. Gut microbiome and serum metabolomics;i. Patient-reported outcomes (PROs): Simplified Chinese version of the EQ-5D-5L, Diabetes Distress Scale [DDS], Chinese version of the Hypoglycemia Fear Survey II-Worry Scale [CHFSII-WS];j. Laboratory safety indicators: liver and renal function.

Detailed protocols for all laboratory measurements, including sample processing, storage conditions, and analytical methods, are summarized in S2 File.

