### 2.10. Statistics and analysis

Efficacy analyses will be performed in the intention-to-treat population. For the primary efficacy endpoint, participants with missing primary endpoint assessments will be considered non-responders using a non-responder imputation approach in the intention-to-treat analysis. Safety analyses will be performed in the safety analysis set. Normality of continuous variables will be assessed using the Shapiro-Wilk test at each time point. Normally distributed data will be presented as mean±standard deviation and analyzed using independent samples t-test (between-group) or paired t-test (within-group). Non-normally distributed data will be presented as median (Q1, Q3) and analyzed using Mann-Whitney U test (between-group) or Wilcoxon signed-rank test (within-group). Categorical data will be expressed as count (percentages) and analyzed using Fisher’s exact test.

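### Two eligibility rules conflict, both can admit participants already on target, and within-group tests against a baseline taken during insulin optimisation cannot isolate a yFMT effect

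*Protocol article*

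**What the plan says.** **Eligibility.** Section 2.3, Table 1 accepts "HbA1c between 7.0 to 14.0% (within past 3 months) or TIR < 70% (14-day CGM within the past month". Section 2.4.1 places the check at Day −17, before the run-in CGM exists: "eligibility will be assessed against all inclusion and exclusion criteria". The Fig 1 note describes a different sequence. After consent, "candidates will undergo a 14-day CGM assessment and HbA1c testing (Day −3", and then "Only those with HbA1c of 7.0–14.0% or CGM-derived TIR below 70% will be enrolled".

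**Baseline.** In the outpatient phase, Day −17 to −3 (section 2.4.2), "Participants will wear CGM and undergo insulin dose optimization", and "participants are instructed to follow a standardized diet according to the Chinese Diabetes Dietary Guidelines (2017". The same section adds that "CGM data from this phase serves as the baseline for glycemic metrics". Section 2.4.4 lets participants in both arms go on adjusting insulin from CGM data.

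**Endpoint and analysis.** The primary endpoint (section 2.5) is the change in the rate of meeting TIR >70% and TBR3.9 <4%, Weeks 10–12 against Day −17 to −3. Section 2.10 analyses it with a logit GEE containing group, time, their interaction and baseline achievement status. For normally distributed continuous variables the section plans "independent samples t-test (between-group) or paired t-test (within-group", with Mann-Whitney and Wilcoxon signed-rank tests otherwise. Significance is two-sided P < 0.05. There are 10 participants per group (section 2.9).

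**The concern.** Three things are at stake.

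1. The trial population is not uniquely defined. Two stated rules use different measurements at different times, and recruitment is already under way (section 2.2).
2. Neither rule asks whether a participant is off the composite target at baseline. Someone already on target can only stay there or lose it. At 10 per arm a few such people reduce sensitivity, and by chance they may fall unevenly between arms.
3. The baseline window is itself a period of changing care. If optimisation has not fully taken effect within that window, or dosing keeps improving afterwards, or people selected for poor control drift back towards their usual level, change from baseline appears in both arms without any action of yFMT. A within-group test cannot separate these causes. The pilot is meant to supply effect-size estimates for a larger trial, so an estimate taken from one arm would carry the problem forward.

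**Working it through.** **What can be reproduced.** The protocol's own figures are only 2 × 10 = 20 participants and an interim look at 10/20 = 50%; both agree. It gives no effect size, SD, target rate or on-target share. Every rate below is an assumption.

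**Step 1: the two rules side by side.**
- Table 1 with section 2.4.1: HbA1c from the past 3 months, or 14-day TIR from the past month; decided at Day −17.
- Fig 1 note: HbA1c at Day −3, or TIR from the run-in CGM; decided after the run-in.

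A person who qualifies on earlier values but has HbA1c below 7.0% and TIR of at least 70% by Day −3 enters under the first rule and not under the second. The reverse can also happen. Under both rules HbA1c of 7.0–14.0% is sufficient whatever the TIR, so someone with run-in TIR >70% and TBR3.9 <4% can be randomised.

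**Step 2: how often, and how unevenly.** With on-target share q, P(at least one of 20) = 1 − (1 − q)^20. The chance that the arms differ by two or more comes from two independent binomials with n = 10.
- q = 5%: 64%, and 11%
- q = 10%: 88%, and 24%
- q = 20%: 99%, and 39%

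**Step 3: lost sensitivity.** Assume off-target participants convert at 20% on placebo and 60% on yFMT, and 80% of on-target participants stay on target in either arm. The Week 12 rate is 0.8q + (1 − q) × conversion, so the difference is (1 − q) × 40 points.
- q = 0: 20% vs 60%, difference 40, exact Fisher power 25%
- q = 20%: 32% vs 64%, difference 32, power 14%
- q = 40%: 44% vs 68%, difference 24, power 8%

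**Step 4: change with no yFMT effect.** A simulation assumed true TIR with mean 60, between-person SD 12, window error SD 6, 70% of people meeting the TBR limit, and a baseline window that sees half of the optimisation gain. Entry was by HbA1c ≥7.0% or run-in TIR <70%. For an optimisation gain of 0, 3, 5 and 8 TIR points:
- on target at baseline: 6.6%, 8.5%, 10.1%, 12.4% (20 × 0.066 = 1.3 to 20 × 0.124 = 2.5 people)
- gain per arm by Week 12: 2.8, 5.2, 7.1, 10.9 percentage points

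**Step 5: the between-arm contrast.** If both arms share the same Week 12 rate, anywhere from 20% to 50%, Fisher's test at 10 vs 10 rejects in 0.8–1.3% of trials. A gain common to both arms does not create a false difference between them.

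**Step 6: what requiring low run-in TIR would do.** In the same simulation, admitting only run-in TIR <70% makes the baseline share 0% but raises the no-effect gain per arm to 7.0, 10.1, 12.6 and 17.2 points. Removing the ceiling in this way increases regression to the mean.

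**The case against.** The strongest reply is that the trial is randomised, double-blind and placebo-controlled, and its primary model is a group-by-time GEE with baseline status as a covariate. Optimisation, diet and regression to the mean act on both arms. This stands: a reader might infer that the primary comparison is biased towards yFMT, and the documents do not support that (Step 5).

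The paired tests are listed for continuous variables, not for the binary primary endpoint, and no passage attributes a within-arm change to yFMT. This also stands, so the point on tests concerns the continuous outcomes and any reading of one arm alone.

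A reader might also infer that an HbA1c up to 3 months old settles enrolment. Table 2 schedules HbA1c at both Day −17 and Day −3, and section 2.4.3 randomises eligible participants after the run-in, so provisional screening with later confirmation is a plausible reading. But the text does not say so, and section 2.4.1 as written applies all criteria at Day −17. The conflict remains, and the 'or' gap is present either way.

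Finally, it is tempting to put a definite size on the harm. If 4 of 20 were on target, a 30-point effect would show as 0.30 × (1 − 0.20) = 24 points, but 4 of 20 has no source. Likewise, with mean TIR 60, SD 15 and within-person correlation 0.7–0.9, 8–13% of those below 70% would later exceed it untreated. That describes people selected on low baseline TIR, covers TIR only, and omits the reverse flow: in the same model 40%, 32% and 23% of those above 70% fall below it (correlation 0.7, 0.8, 0.9). Without selection on TIR the two flows cancel.

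**Conclusion.** The point holds in limited form. The eligibility rules contradict each other on measurement and timing. Either can admit participants who cannot gain on the primary endpoint. Within-group tests against this baseline are not evidence about yFMT. The between-arm contrast is unbiased in expectation; what it risks is reduced sensitivity and chance imbalance. The size cannot be fixed from the documents. Under the stated assumptions the ceiling involves roughly one to three of 20 participants, and the change per arm with no yFMT effect is about 3 to 11 percentage points. These figures depend on the assumed TIR distribution, TBR share and optimisation gain. The power figures in Step 3 use larger shares and show direction more than expected loss.

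**What to change.** - Reconcile Table 1, section 2.4.1 and the Fig 1 note into one eligibility rule with one decision time point, and state which measurement each threshold refers to.
- In section 2.10, drop the paired t and Wilcoxon signed-rank tests as inference and report within-arm change descriptively.
- Base efficacy conclusions, and the effect sizes carried to the next trial, only on between-arm contrasts adjusted for baseline.
- Report by arm the number already on target at baseline.

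Do not add an entry requirement to be off target while recruitment is under way. It would increase regression to the mean, make baseline achievement 0% in both arms, and leave the stated GEE with no baseline events and a constant covariate. It would also mix two populations among 20 people.

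The cost is a short amendment to align the text and fewer P values in the report. No extra data are needed.

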**Exclusion Criteria**	
1	Treatment with any anti-hyperglycemic medications other than insulin
2	Continuous use of antimicrobial agents, probiotics, intestinal microecological modulators, or other medications with potential impact on gut microbiota for >3 days within 3 months prior to enrollment;
3	Occurrence of acute diabetic complications (diabetic ketoacidosis, hyperosmolar hyperglycemic state) within 1 month prior to enrollment;
4	Coexisting gastrointestinal diseases (including persistent vomiting, confirmed/suspected gastrointestinal obstruction, short bowel syndrome, inflammatory bowel disease, active major gastrointestinal bleeding, gastrointestinal perforation, high-output intestinal fistula, severe diarrhea, significant fibrotic intestinal stenosis, fulminant colitis, or toxic megacolon), history of gastrointestinal surgery (such as gastrectomy, pelvic anastomosis, colostomy, or other digestive system procedures), malignancy, or sepsis;
5	Coexisting severe cardiovascular or cerebrovascular diseases, hepatic or renal disorders, hematopoietic system diseases, severe immunosuppression, or congenital/acquired immunodeficiency diseases;
6	Recent administration of high-risk immunosuppressive or cytotoxic medications: e.g., rituximab, doxorubicin, or medium-to-high dose corticosteroids (prednisone ≥20 mg/day) for more than 4 weeks;
7	Use of closed-loop systems or sensor-augmented pumps within the past 3 months;
8	Concurrent participation in another randomized clinical trial;
9	Pregnancy, lactation, or planned pregnancy during the study period in female participants;
10	Inability to adhere to the recommended intervention and follow-up schedule for any reason.

**Abbreviations:** T1DM, type 1 diabetes mellitus; HbA1c, glycated hemoglobin; MDI, multiple daily insulin injections; TDD, total daily insulin dose.

### 2.4. Procedures

#### 2.4.1. Screening (Day −17).

Screening (Day −17, Outpatient): Informed consent will be obtained, and eligibility will be assessed against all inclusion and exclusion criteria. Eligible participants will be provided with a CGM device.

#### 2.4.2. Run-in Period and Baseline Assessments (Day −17 to Day 0).

This period standardizes participants’ status prior to intervention and consists of two phases:

*Outpatient Phase* (Day −17 to −3): Participants will wear CGM and undergo insulin dose optimization. During this period, participants are instructed to follow a standardized diet according to the Chinese Diabetes Dietary Guidelines (2017). Dietary adherence is monitored through food records and regular follow-up communications via WeChat or outpatient visits. CGM data from this phase serves as the baseline for glycemic metrics, including TIR, TBR3.9, glucose management indicator (GMI), coefficient of variation (CV), and other metrics.

*Inpatient Phase* (Day −3–0): Participants are hospitalized for baseline assessments and bowel preparation:

(1) Baseline Assessments (Completed by Day −3) include:a. Demographics and clinical parameters: age, sex, T1DM duration, anthropometrics (height, weight, waist-to-hip ratio [WHR]), vital signs (blood pressure, pulse), and comprehensive medical/medication history;b. Glycemic and lipid profiles: fasting plasma glucose, 2-hour postprandial glucose via Mixed-Meal Tolerance Test [MMT], HbA1c, total cholesterol (TC), triglycerides (TG), low-density lipoprotein cholesterol [LDL-c], and high-density lipoprotein cholesterol [HDL-c];c. β-cell function and insulin sensitivity (fasting/stimulated 2-hour C-peptide during Mixed-Meal Tolerance Test [MMT 2h CP], estimated glucose disposal rate [eGDR]);d. Diabetic autoantibodies: Glutamic Acid Decarboxylase Autoantibodies [GADA], Insulinoma-associated antigen-2 autoantibodies [IA‑2A], Islet cell autoantibodies [ICA];e. Inflammatory markers: white blood cell count [WBC], High-Sensitivity C-reactive protein [hs-CRP], erythrocyte sedimentation rate [ESR], procalcitonin [PCT], and cytokines [TNF-α, IL-1β, IL-8, IFN-γ];f. Intestinal Barrier-Related Antibodies: Anti-Lipopolysaccharide [Anti-LPS], Anti-Occludin;g. Immune marker: Treg/Th17 ratio;h. Gut microbiome and serum metabolomics;i. Patient-reported outcomes (PROs): Simplified Chinese version of the EQ-5D-5L, Diabetes Distress Scale [DDS], Chinese version of the Hypoglycemia Fear Survey II-Worry Scale [CHFSII-WS];j. Laboratory safety indicators: liver and renal function.

Detailed protocols for all laboratory measurements, including sample processing, storage conditions, and analytical methods, are summarized in S2 File.

(2) Bowel Preparation: from Day −3, participants receive oral rifaximin (0.2 g per dose, four times daily), with bowel preparation using a polyethylene glycol solution performed on Day 0.

